## Methods/Design

### Experimental Approach

The present project and study protocol were registered in clinicaltrials.gov (ID: NCT03724461, October 30th, 2018) and approved by the Clinical Research Ethics Committee of the Complejo Hospitalario de Toledo (Spain). The study protocol will be conducted following the SPIRIT (Standard Protocol Items: Recommendations for Interventional Trials) statement (Chan et al., 2013). The intervention and data collection will be conducted at the University of Castilla-La Mancha, Toledo (Spain). This is a within-person randomized trial, including an 8-week control period followed by 12 weeks of PRT (Figure 1). The mean changes observed during the 8-week control period will be quantified to determine the possible extent of spontaneous changes in all outcome measures. After completing the control period, the participants will be randomized to one of the following study arms based on the treatment applied to their lower-limbs during the 12-week PRT program: (i) one leg will perform a light-load PRT and the other leg will not perform any exercise; (ii) one leg will perform a heavy-load PRT and the other leg will not perform any exercise; and (iii) one leg will perform a heavy-load PRT and the other leg will perform a light-load PRT. Assessments will be conducted at baseline (week 0), at the end of the control period (week 8), and following the 12-week PRT (week 20).

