### Participants

The sample size was determined by an *a priori* power analysis using G^∗^Power v3 software for MS Windows^®^ (Faul et al., 2007). The effect size value used for calculations was *d* = 0.25 based on a previous study comparing peak power adaptations after a 12-week heavy- vs. light-load PRT in older adults (de Vos et al., 2005). Then, we considered three levels for the between-subject factor (i.e., one for each study arm) and three levels for the within-subject factor (i.e., three repeated measures) setting the alpha error probability at 0.05, a 1−β of 0.95 and assuming a correlation among repeated measures of *r* = 0.8. The model indicated a minimum total sample size of 24 individuals, but considering a 25% dropout rate, we have decided to enroll at least 30 participants in total. People aged 65 years and over, non-institutionalized and without serious mobility limitations will be encouraged to participate. Principally, the volunteers will be recruited among participants involved in non-exercise studies previously conducted by our research group, local advertisements posted in public places and informative talks about healthy aging. After accepting to participate, the volunteers will undergo a physical examination by a geriatrician. The criteria for exclusion are: (i) frailty status (Fried et al., 2001) or low levels of physical function (i.e., Short Physical Performance Battery <7 points) (Guralnik et al., 1994), (ii) neurological, musculoskeletal, or other disorders that might preclude subjects from completing the resistance training and all performance tests, (iii) uncontrolled hypertension, unstable or exercise-induced angina pectoris or myocardial ischemia or any other medical condition that would interfere with testing or increase subjects’ risk of complications during exercise, (iv) history of regular resistance exercise during the previous 3 years, and (v) total or partial knee replacement (i.e., prosthesis). All participants will be informed orally and in written form about the purpose, procedures, benefits, risks, and potential discomfort related to study participation before signing a consent form. This study will be conducted in accordance with the Helsinki declaration.

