### Randomization and Allocation of Participants

After completing the control period, the participants will be stratified by their sex and 1RM values and randomly allocated in equal numbers to the three intervention groups. Then, the treatment applied to the subjects’ legs will be determined by coin toss.

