### Statistical Analysis

Data will preferentially be presented as mean ± standard deviation. Normality of distribution will be assessed by the Shapiro–Wilk test and log-transformed in case of non-normal distribution. As preference, the outcomes will be registered as the absolute (Post – Pre) and relative [(Post – Pre)/Pre] change during the 8-week control period and the 12-week PRT program. Given the hierarchical structure and correlated data contained in our investigation (each participant will contribute to observations in two different groups), the existence of partially paired data must be considered for comparison purposes. Thus, linear mixed effect models will be used to assess the goals proposed for the present investigation. To assess the adaptations provoked by two volume × load-matched PRT programs using heavy vs. light loads in older adults (goal 1), changes noted in the legs undergoing HL-PRT and LL-PRT (i.e., week 20-week 8) and those noted in the same legs during the control period (i.e., week 8-week 0) will be compared with treatment (HL-PRT vs. LL-PRT vs. control) as a fixed factor, participants as a random factor and baseline values as a covariate. To investigate the adaptations provoked by heavy- vs. light-load PRT on the contralateral limb in older adults (goal 2), changes noted in the contralateral non-exercising legs of those legs performing either HL- or LL-PRT (i.e., week 20-week 8) and those noted in the same legs during the control period (i.e., week 8-week 0) will be compared with treatment (HL-PRT vs. LL-PRT vs. control) as a fixed factor, participants as a random factor and baseline values as a covariate. The models will be calculated considering maximum likelihood estimation and the best-fitting covariance structure. Bonferroni corrections will be applied for the *post hoc* pairwise comparisons and the Cohen’s *d* effect sizes will be calculated and classified as trivial (0.20), small (0.20–0.49), moderate (0.50–0.79), and large (>0.8) (Cohen, 1988). Potential adverse events and drop-outs will be compared between groups by Chi-squared tests. All statistical analyses will be performed using IBM SPSS Statistics for Windows Version 24.0 (IBM Corp. Armonk, NY, United States), and the level of significance will be set at α = 0.05.

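### Goal 2 takes its control change from the untrained legs only (20 of 60), so the load-versus-control contrasts are valid but less precise than the collected data allow

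*Protocol article*

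**What the plan says.** The protocol article's Experimental Approach puts every participant through an 8-week control period before a 12-week training period. Its stated purpose covers all outcomes and is not limited to particular legs: "The mean changes observed during the 8-week control period will be quantified to determine the possible extent of spontaneous changes in all outcome measures". Allocation comes later: "After completing the control period, the participants will be stratified by their sex and 1RM values and randomly allocated", with three arms of equal size (section on randomization and allocation). A coin toss then decides which leg gets which treatment. Arms (i) and (ii) each leave one leg untrained. Arm (iii) trains both legs.

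The Statistical Analysis section sets up one linear mixed model per goal, each with three treatment levels: heavy load, light load and control. For goal 2 the control level comes from the week 0 to week 8 changes of the same untrained legs that supply the training-period rows: "contralateral non-exercising legs of those legs performing either HL- or LL-PRT (i.e., week 20-week 8) and those noted in the same legs". Goal 1 applies the same rule to the trained legs. Participant is the only random factor named, baseline is a covariate, and pairwise comparisons are Bonferroni-corrected. No power is given for goal 2.

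**The concern.** After week 8 no participant is wholly untrained, so the control period is the only comparator that can show whether the untrained leg improves at all. The Discussion expects to see cross-education and expects little or no difference between loads. The expected positive result therefore rests on the two load-versus-control contrasts, each with only 10 untrained legs on the training side.

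During weeks 0 to 8 nothing distinguishes a leg that will later be untrained from any other leg, because neither arm nor leg has been assigned. All legs share one expected spontaneous change. Restricting the goal 2 control mean to the later-untrained legs makes it noisier than necessary. The result is wider intervals and a greater chance of missing real cross-education.

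**Working it through.** **The plan's own figure.** Inputs from the Participants section: "The effect size value used for calculations was *d* = 0.25"; "assuming a correlation among repeated measures of *r* = 0.8"; "three levels for the between-subject factor (i.e., one for each study arm) and three levels for the within-subject factor"; "setting the alpha error probability at 0.05, a 1−β of 0.95". For the arm-by-visit interaction, lambda = f² × N × m/(1 - r) = 0.25² × 24 × 3/0.2 = 22.5 with 4 and 42 df. This gives power 0.965 at N = 24 and 0.933 at N = 21, so "The model indicated a minimum total sample size of 24 individuals" reproduces when 0.25 is entered as Cohen's f. Then 24 × 1.25 = 30. This calculation does not address the goal 2 contrasts. Only the 30 and the r = 0.8 are used below.

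**Leg counts at N = 30, equal arms.** All legs: 60. Untrained legs: 10 + 10 + 0 = 20. Of the other 40, 20 are the trained legs of the same 20 participants and 20 belong to the 10 participants of arm (iii).

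**Variance of one load-versus-control contrast in goal 2.** The unit is the SD of a change score, taken as equal in both periods. Let ρ be the correlation between the control and training changes of the same leg, c the correlation between a person's two legs in the same period, and cρ the correlation across both leg and period. Generalised least squares gives

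Var = (1 - ρ²)/10 + (1 - ρ)² × Var(control mean),

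where Var(control mean) = 1/20 with the same legs and (1 + c)/60 with all legs.

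**Values of ρ.** With constant r = 0.8 across visits, the covariance of the two changes is 0.8 - 1 - 0.8 + 0.8 = -0.2 and each variance is 2 × (1 - 0.8) = 0.4, so ρ = -0.5. If the week 0 to week 20 correlation decays to 0.64, the covariance is -0.04 and ρ = -0.1. If people differ consistently in trend, ρ can be positive. The article gives neither ρ nor c, so both are varied (c = 0.3 to 0.7).

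Example at ρ = -0.5, c = 0.5:
- Same legs: 0.75/10 + 2.25/20 = 0.1875, SE 0.433.
- All legs: 0.75/10 + 2.25 × 1.5/60 = 0.1313, SE 0.362.

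| ρ | SE, same 20 legs | SE, all 60 legs (c = 0.3 to 0.7) | Reduction | 80% power becomes |
|---|---|---|---|---|
| -0.5 | 0.433 | 0.352-0.372 | 14-19% | 91-94% |
| -0.1 | 0.399 | 0.354-0.365 | 9-11% | 87-90% |
| 0 | 0.387 | 0.349-0.358 | 7-10% | 86-89% |
| +0.3 | 0.340 | 0.319-0.324 | 5-6% | 84-85% |

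The last column is a normal approximation at two-sided 0.05/3 (critical value 2.394). The true effect is set so that the same-leg analysis has 80% power: power = Φ[(2.394 + 0.842) × SE(same)/SE(all) - 2.394].

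**Other contrasts.** The heavy-versus-light SE in goal 2 is identical with 20 or 60 control legs (0.387 at ρ = -0.5, 0.447 at ρ = 0). In goal 1, moving from 40 to 60 control legs shortens the load-versus-control SE by 3-8% at ρ = -0.5, 2-4% at ρ = 0 and 1-3% at +0.3.

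**The case against.** The case for leaving the plan alone is substantial. The same-leg control is stated openly, applied to both goals, and consistent with the Introduction's argument for control periods and within-person comparison. It introduces no bias. Goal 2, as worded, compares heavy with light load, and that contrast gains nothing. The gain elsewhere depends on correlations that the article does not report: r = 0.8 is a planning input, and the planned baseline covariate changes the relevant correlation. Adjusting each change for its own starting value under constant r = 0.8 gives a residual ρ of (0.8 - 0.8 - 0.64 + 0.512)/0.36 = -0.36, for which the reduction is 12-16%. Pooling needs more covariance structure than a participant effect, and it does not address the comparison of an 8-week change with a 12-week change.

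All of this stands, and it makes the point one of efficiency. It does not remove the point: the reduction is positive at every correlation tried, and the contrasts that gain are the only ones that can show cross-education.

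Three stronger readings are tempting but not supported:
- That two thirds of the control data are thrown away. The other 40 legs supply the goal 1 control. They are unused only in goal 2, and because 20 of them belong to participants already in that model, the information lost is much less than two thirds.
- That pairing within a leg can only add variance. That is so when ρ is negative. At ρ = +0.3 the same-leg SE is 0.340, against 0.387 at ρ = 0, so pairing helps.
- That the comparison of loads in goal 2 is weakened. It is not.

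**Conclusion.** The point holds as a precision loss in the goal 2 load-versus-control contrasts, not as an error or a contradiction. With 10 participants per arm and a between-leg correlation of 0.3 to 0.7, using all legs reduces the SE of each contrast by 14-19% at ρ = -0.5, by 7-10% at ρ = 0 and by about 5-6% at ρ = +0.3. The calculation assumes equal variances in the two periods, no dropout and, in the table, no baseline covariate. That pooling is unbiased in expectation follows from assigning participants and legs after the control period. The change is worth making because goal 2 has few untrained legs and no stated power, and the data are collected anyway.

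**What to change.** In the Statistical Analysis section, state that the control level is estimated from the week 0 to week 8 changes of all legs of all participants. This matters chiefly for goal 2, where it adds control-period rows from the trained legs of arms (i) and (ii) and from both legs of arm (iii). The same wording can be used for goal 1, where the gain is small. Leave the training-period rows as planned. Specify a covariance structure for leg within participant and for the two periods of the same leg. Keep the same-leg comparison as a sensitivity analysis, and settle the choice before outcome data are examined so that the control set cannot appear data-driven.

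The cost is a few sentences of analysis wording and a slightly more complex covariance model for about 30 participants. The control mean also ceases to be restricted to the same legs. No extra measurement or recruitment is needed.

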### Primary Outcomes

#### Maximal Isometric Force (MIF) and Rate of Force Development (RFD) of the Knee Extensors

For isometric strength tests, participants will be seated on a custom-built isometric chair (Telju Fitness, Spain) with knee and hip angles of 90° and 120°, respectively (180° full extension). An ankle brace together with a steel cable with minimal compliance will be used to connect the lower leg to a strain gauge cell (Linear Force SmartLead, Noraxon, United States) to register knee extension force at 1,500 Hz. Then, participants will be instructed to perform several maximal voluntary isometric contractions (MVIC), extending their knee as fast and strong as possible and holding the contraction for 3 s after the cue “ready, set, go!.” Strong verbal encouragement and visual feedback will be given in each attempt to ensure maximal efforts. Five adequate trials (separated by 60 s) will be acquired. Then, the MIF will be determined as the highest force value registered, and the RFD will be calculated as the linear slope of the time-force curve between 0–50, 0–100 and 0–200, 0–400 ms and at the maximal point of the time-RFD curve (RFD_max_).

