#### Force-Velocity Relationship and Maximal Dynamic Strength in the Unilateral Leg Press Exercise

The assessments will be conducted on a horizontal leg press device (Selection MD, Technogym, Italy) instrumented with a force plate (Type 9286BA, Kistler, Switzerland) and a linear position transducer (Linear encoder, Chronojump Boscosystem, Spain). A detailed description and validation of the systematic procedure that will be followed to obtain the force-velocity relationship and maximal dynamic strength in older adults has been previously published (Alcazar et al., 2017). Briefly, the participants will perform two sets of two repetitions with the starting load equivalent to 40% of their body mass being gradually increased (5–20 kg increments) until the 1-RM is reached (failure was defined as not being able to lift a load within two attempts). From the starting position (knee and hip joint angles of 90° and 70°, respectively; full extension = 180°), the repetitions will be executed as fast as possible during the concentric phase, whereas self-preferred eccentric velocity will be demanded to warrant maximal performance in the subsequent repetition. The processing of force and velocity signals has been described previously (Rodriguez-Lopez et al., 2020). Shortly, force and velocity values from the most powerful attempts of each load (i.e., highest mean power value) will be fitted in a linear model, distinguishing between first and second repetitions (i.e., concentric-only vs. eccentric-concentric performance). Then, the theoretical maximal isometric force and maximal velocity with no load will be estimated through extrapolation of the linear regression line (force- and velocity intercepts, respectively). In addition, the maximal muscle power as well as the force and velocity at which it is produced will be determined (Alcazar et al., 2017).

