#### Mid-Thigh Muscle Size and Architecture

The participants will lie on an examination table in supine position and with the legs slightly flexed with the aid of a foam roller placed beneath the knee. To allow for fluid shifts to occur, this position will be held for 15 min before examination. Brightness mode ultrasound (MyLab 25, Esaote Biomedica, Genova, Italy) images will be taken with a 50 mm, 10–15 MHz linear-array probe. The scans will be acquired at 50% of the distance between the greater trochanter and the inferior border of the lateral condyle of the femur. For muscle size quantification, three transversal panoramic scans of the rectus femoris and the vastus lateralis muscles will be obtained using the extended field of view image stitching technique. For this purpose, the examiner will acquire images by moving the prove from the medial aponeurosis of the rectus femoris to the lateral border of the vastus lateralis at constant velocity. Then, three longitudinal images of the vastus lateralis will be obtained with the probe positioned at an individually determined optimal location (characterized by parallel aponeuroses and consistency of the fascicle orientation) and aligned with the fascicle plane. Abundant transmission gel will be applied to ensure acoustic coupling with minimal pressure to avoid muscle deformation. All scans will be subsequently analyzed using Fiji image analysis software (Schindelin et al., 2012). For measurements of muscle size of the rectus femoris and vastus lateralis, the muscles’ aponeuroses will be traced to quantify the cross-sectional area. The vastus lateralis muscle architecture will be analyzed through the Simple Muscle Architecture Analysis tool for Fiji (Seynnes and Cronin, 2020). Basically, this is an automated analysis process that highlights aponeuroses and fascicles to obtain the dominant fascicle orientation (i.e., pennation angle) and estimate fascicle length.

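### No single primary variable or change scale is fixed among 21 listed; error is controlled only across the three pairwise contrasts, which also puts heavy vs light load at 0.0167

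*Protocol article*

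**What the plan says.** The Primary Outcomes section of the protocol article has three subsections.

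- **Isometric knee extension:** maximal isometric force and rate of force development (RFD). For the latter, "the RFD will be calculated as the linear slope of the time-force curve between 0–50, 0–100 and 0–200, 0–400 ms", plus the maximum of the RFD curve.
- **Leg press:** 1-RM, the force and velocity intercepts of a linear fit, maximal muscle power, and the force and velocity at which that power occurs. The fit is made "distinguishing between first and second repetitions (i.e., concentric-only vs. eccentric-concentric performance").
- **Ultrasound:** cross-sectional area of two muscles, and vastus lateralis pennation angle and fascicle length ("The vastus lateralis muscle architecture will be analyzed through the Simple Muscle Architecture Analysis tool for Fiji").

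No variable is ranked above another. The Participants section sizes the trial on one kind of outcome, peak power: "The effect size value used for calculations was *d* = 0.25", "setting the alpha error probability at 0.05, a 1−β of 0.95".

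The Statistical Analysis section compares changes in a mixed model with a three-level treatment factor (heavy load, light load, control). On multiplicity it says "Bonferroni corrections will be applied for the *post hoc* pairwise comparisons" and "the level of significance will be set at α = 0.05". On scale it says "the outcomes will be registered as the absolute (Post – Pre) and relative [(Post – Pre)/Pre] change".

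**The concern.** The stated multiplicity rule covers three contrasts within a variable. Nothing covers the 21 variables, where the number of tests is much larger. A chance result on the force side, the velocity side or the ultrasound side could be reported as a load-specific adaptation on a primary outcome. Because no change scale is fixed for testing, that choice could also be made after the data are seen.

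The rule also bears on the main question. Goal 1 is heavy vs light load, yet this contrast is one of three post hoc pairs, each at 0.05/3. The plan therefore leaves error across primary variables open while charging the contrast of most interest.

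**Working it through.** **1. The plan's own sample size.** Inputs from Participants: 3 arms, 3 repeated measures, correlation 0.8, alpha 0.05, power 0.95, effect 0.25. For the arm-by-time interaction, with 0.25 entered as Cohen's f:

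- noncentrality = N·m·f²/(1−ρ) = 24 × 3 × 0.0625/0.2 = 22.5
- df = (3−1)(3−1) = 4 and (24−3)(3−1) = 42
- power = 0.965 at N = 24, and 0.933 at N = 21

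The stated 24 reproduces. It is a calculation for one outcome at 0.05.

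**2. Count of primary variables (goal 1 only).**

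| Source | Variables |
|---|---|
| Maximal isometric force | 1 |
| RFD: four windows + maximum | 5 |
| Force-velocity: 5 quantities × 2 repetition types | 10 |
| 1-RM | 1 |
| Cross-sectional areas | 2 |
| Pennation angle, fascicle length | 2 |
| Total | 21 |

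If the optimum is read from the linear fit, force at maximal power is half the force intercept and velocity at maximal power is half the velocity intercept. Those 2 × 2 = 4 variables then repeat tests already made, which leaves 21 − 4 = 17.

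**3. Chance of at least one false positive if no variable has a true effect.** For independent tests this is 1 − (1 − α)^k.

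- Three-level test at 0.05: 1 − 0.95^21 = 0.66; with 17 variables, 1 − 0.95^17 = 0.58
- Heavy vs light at 0.05/3 = 0.0167: 1 − (1 − 0.0167)^21 = 0.30; with 17, 0.25

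The correlations among variables are not given, so they are assumptions here. Simulation of 21 two-sided z-tests (400,000 draws) gives:

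| Common correlation | At 0.05 | At 0.0167 |
|---|---|---|
| 0 | 0.66 | 0.30 |
| 0.3 | 0.56 | 0.24 |
| 0.5 | 0.43 | 0.19 |
| 0.7 | 0.30 | 0.13 |
| 0.9 | 0.16 | 0.06 |

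Three blocks of 6, 11 and 4 variables, with correlation 0.5-0.8 within and 0.2-0.3 between blocks, give 0.35-0.52 and 0.15-0.23. The expected number of false positives is 21 × 0.05 = 1.05 at the three-level test and 21 × 0.0167 = 0.35 for heavy vs light, whatever the correlation.

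**4. Power for heavy vs light at 0.0167 and 0.05.** Assumptions: 10 per arm, no dropout, and residual SD √(1 − 0.8²) = 0.6 after adjustment for the pre-training value, using the protocol's 0.8. The between-leg correlation r is not in the document. The arm that trains both legs gives a paired variance of 2 × 0.36 × (1 − r)/10. The other two arms give an unpaired variance of 2 × 0.36/10 = 0.072. Weighting by inverse variance at r = 0.5: 1/(1/0.036 + 1/0.072) = 0.024, so SE = 0.155 SD. Noncentral t with 26 df, true difference 0.5 SD:

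| r | SE | Power at 0.0167 | Power at 0.05 |
|---|---|---|---|
| 0 | 0.190 | 0.54 | 0.72 |
| 0.5 | 0.155 | 0.74 | 0.87 |
| 0.8 | 0.110 | 0.97 | 0.99 |

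With 8 per arm (20 df) and r = 0.5, the pair is 0.61 and 0.78.

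**The case against.** Several objections have force.

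- **The 66% figure.** A reader might infer that a false heavy-vs-light claim is more likely than not. The documents do not support that. The 66% assumes 21 independent tests at 0.05, whereas this contrast runs at 0.0167. Its ceiling is about 30%, or 25% if four force-velocity variables are redundant. The Bonferroni step that costs power also limits this error.
- **Two scales.** A reader might infer that every variable is tested as both absolute and relative change. The text says only that both forms are recorded. The fault is that neither is named as the tested one.
- **What was powered.** A reader might infer that the trial was sized for heavy vs light. It was sized for a three-arm by three-time model. The heavy-vs-light study only supplied the effect size.
- **Power loss.** It depends on an assumed between-leg correlation and is small at 0.8.
- **Bonferroni is valid.** It is conservative for three pairs but not an error.
- **A separate analysis plan may add a hierarchy.** That cannot be seen. But the article does state a multiplicity rule, and the rule stops at the pairwise contrasts.

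All of these narrow the size of the problem. None supplies a named primary variable, a fixed scale or any control across variables.

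**Conclusion.** The point stands as a cheap improvement and not as a flaw that invalidates the trial. The article lists 21 co-equal primary variables (about 17 distinct under the linear-fit reading), controls error only within each, and fixes no tested change scale. The chance of at least one false-positive primary result is about 16-66% for the three-level test and about 6-30% for heavy vs light. These ranges run from common correlation 0.9 to independence. Only very high correlation brings the heavy-vs-light figure close to 5%.

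The goal 1 contrast meanwhile pays an avoidable price. The gain from testing it at 0.05 runs from 0.02 to 0.18 in power at a 0.5 SD difference, under the assumptions shown (residual SD 0.6, 10 per arm, no dropout).

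**What to change.** - Name one primary variable. Leg-press maximal muscle power is the natural choice, because it is the type of outcome behind the sample size. Fix one repetition type and one change scale for it.
- Name heavy vs light load as the primary contrast, at two-sided 0.05.
- Make the other listed variables secondary. Either test them under Holm or a fixed sequence, or report them with confidence intervals and no claim of significance.
- Within a variable, replace Bonferroni by the closed test for three treatments (the three-level test at 0.05, then pairs at 0.05 only if it is significant) or by Holm.

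The rest of the mixed model can stay as it is for this purpose.

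Cost: analysis wording. No participants, visits or measurements are added. Fewer variables can be headlined as primary, and the registry entry may need updating.

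The alternative, keeping all 21 as primary with Bonferroni across them (0.05/21 = 0.0024 each), is dearer. Under the protocol's own interaction model it needs N = 36 for power 0.956, against 0.72 at N = 24 and 0.88 at N = 30.
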